### Data collection and management

#### Data collection: primary objectives

Our study staff in the three study clinics identifies HIV-1-negative pregnant women in the delivery rooms. Potential participants are approached and informed about the study. Following a live birth, study procedures are explained to the women, and babies of those providing informed consent are enrolled and then randomized to either the intervention or comparison arm by research assistants, using the cell phone-based application described above. For enrolled infants, data will be collected using questionnaires on day 1, and on days 3, 7, 14 and 28 after birth (Fig. 1).

**Fig. 1 Fig1:**

Time schedule for study procedures (Standard Protocol Items: Recommendations for Interventional Trials (SPIRIT) figure)

Using a standardized approach (distance, light, etc.), at each of the above-defined visits and at any additional contact, data will be collected on umbilical cord stump infection and digital pictures are captured of the umbilical cord stump with its surrounding skin. Participating women will be invited to bring their children to the study clinics on the scheduled dates for data collection. Home visits will be conducted for women unable to come to the health facilities for the scheduled interviews (Fig. 1).

To capture severe illness, mothers and other caregivers will be informed about its symptoms and signs, and will be encouraged to contact the study clinic in case the baby develops any of the symptoms. Each mother is provided with a durable note book in which she or an attending health care worker are requested to note down all relevant events for the child. A child who comes to a clinic with such symptoms or signs will be examined by a study nurse/midwife and will receive the appropriate treatment. If the child does not attend after the mother/caregiver has informed the study team of such symptoms/signs or for a scheduled visit, the study nurse/midwife will make a visit to the child’s house. If the nurse/midwife classifies the condition as possible severe illness, a study physician will be called to examine the child. If the physician classifies the child as having severe illness, they will collect a blood specimen for blood culture (using BACTEC) and for a septic screen (C-reactive protein (CRP), total lymphocyte count, differential count, band cell: neutrophil count ratio) as soon as possible. A repeat specimen will be collected again for CRP between 24 and 48 h. The study team will do its utmost to obtain specimens for such a septic screen from as many infants with signs of severe illness as possible. With the consent of the parents, all children with neonatal sepsis are admitted to the National Referral and Teaching Hospital (Mulago Hospital) where they are managed according to the national guidelines. In the event of a neonatal death, it is our experience that a mother may call spontaneously to inform the study team of why she is not coming to the next scheduled visit. However, in most cases, she will simply not turn up; in that case, the death will be captured when she is contacted because of a missed visit. A “verbal autopsy” for all neonatal deaths will be conducted as soon as it is socially acceptable to maximize recall without socially offending the participants. We will assess the cause of death using a standard World Health Organization (WHO) Verbal Autopsy Questionnaire that has been validated in Uganda. The questionnaire has both open-ended questions (for verbatim narratives) and closed-ended questions, and we will employ a standard algorithm to determine the likely cause of death [12]. Two independent reviewers will examine the verbal autopsies and assign a likely cause of death. In event of divergent conclusions, a third reviewer will be requested to provide a third review.

### Project management

The study will be conducted as a collaboration between the College of Health Sciences, Makerere University and the Center for International Health, University of Bergen. The study will be guided by a Steering Committee which will include the principal investigator (PI) and the co-principal investigator (Co-PI) supported by the other co-investigators and a newly established Participatory Scientific Advisory Group (PSAG). The Steering Committee (VN and HS) is responsible for the conduct and coordination of the study. The Steering Committee will be the decision-making body for all scientific and administrative aspects. It will send reports to the funding agency, ethical committees and regulatory bodies. The SC will meet on regular conference calls with at least two face-to-face meetings annually. The study is registered with ClinicalTrials.gov (identifier: NCT02606565).

### Quality control

All data is collected using standardized questionnaires and forms on an ODK platform using Android cell phones. The study nurses were trained extensively in all the routines and how to fill the questionnaires and Case Report Forms before study implementation. In particular, they received training on the assessment and grading of omphalitis using audio-visual aids and pictorials by faculty members at the College of Health Sciences, Makerere University. Newborns with moderate to severe omphalitis or severe illness are immediately referred to the nearest government health unit. At least one scientist/medical officer is employed by the project to supervise the field team and ensure good-quality data. To minimize losses to follow-up, the following measures are taken: (1) careful screening of study participants for eligibility before enrollment, (2) consenting participants are provided with a transport refund that covers their costs to and from the health facility, (3) contact telephone numbers are obtained from each consenting participant and reminders are made prior to each scheduled date and (4) each study site has a dedicated tracer with good knowledge of the study site geography. Importantly, detailed information on the physical location/address of the participants’ homes is collected at enrollment to help with tracing mothers who do not attend for study visits. Research assistants (who are licensed nurses or midwives) have been, and are being, rigorously trained to obtain informed consent from study participates. They also receive training on all study tools which have been pretested and standardized to minimize information biases. The capture of digital images of the umbilical cord stump and surrounding skin will enhance the diagnostic specificity of reported omphalitis cases.

### Data analyses

Baseline characteristics of the mothers, their households and the newborns will be compared between the intervention and comparison arms to check for comparability and identify potential confounders. Continuous variables will be summarized using means, medians, standard deviations and interquartile ranges while percentages will be used for categorical variables.

Analysis for both primary objectives will be based on intention-to-treat. Therefore, all infants randomized and enrolled into the study will be included in the final analysis regardless of whether CHX was applied to their umbilical cord stump and surrounding skin or not (Fig. 2: flow chart and Additional file 1: Standard Protocol Items: Recommendations for Interventional Trials (SPIRIT) Checklist). The risks of omphalitis and severe illness in the intervention arm will be compared to those in the comparison arm using binomial regression with a log link to obtain risk ratios (RR). Multivariable analysis will be used to take into account potential confounding. Only confounders whose inclusion in the model results in a substantial (>5%) change in the estimate of the main outcome will be maintained in the final model. Percent protective efficacy will be calculated as (1 − RR) × 100.

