### Randomization

For each of the three health centres, a computer-generated random sequence list with permuted blocks of varying size (4, 6 or 8) was generated by CISMAC scientist [name], who is otherwise not involved in the trial. Based on this sequence, children are randomly allocated to intervention or comparison arms in a 1:1 ratio. Concealment is by a cell phone-based application that yields the trial arm allocation only after consent for inclusion has been confirmed.

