### Background characteristics and potential confounders

Using questionnaires and available records, data will be collected on several potential individual-level confounders. These include: maternal age, maternal education, antenatal care attendance, iron supplementation during pregnancy, antibiotic use during the last weeks of pregnancy, premature rupture of membranes, signs of chorioamnionitis, wealth, household size, parity, tetanus vaccination, gestational age, singleton or multiple birth, sex of the infant, birth weight, use of a clean delivery kit, prelacteal feeds, breastfeeding initiation time, infant’s receipt of colostrum, and Bacille Calmette-Guérin (BCG) vaccination. To further describe the population from which our participants are derived and to adjust for any contextual level confounders, we collect data using questionnaires on group/contextual-level factors such as the presence of electricity in the community, and residence (rural versus urban).

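### Keeping covariates only if they move the risk ratio by more than 5% is a confounding rule in a randomised trial: it gives up modest precision and lets outcome data decide the covariate set

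*Protocol article*

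**What the plan says.** All of the analysis rule is in the protocol article, Data analyses. The arms' baseline characteristics "will be compared between the intervention and comparison arms to check for comparability and identify potential confounders". Both primary outcomes are then compared by log-binomial regression, giving risk ratios. Next, "Multivariable analysis will be used to take into account potential confounding", followed by the retention rule: "Only confounders whose inclusion in the model results in a substantial (>5%) change in the estimate of the main outcome will be maintained". Protective efficacy is then computed from the RR.

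Two other sections bear on it. Under Background characteristics and potential confounders, "data will be collected on several potential individual-level confounders", and 20 such factors are listed, plus contextual ones. Under Randomization, each of the three health centres has its own permuted-block list, so allocation is stratified by centre. Data analyses does not mention centre, retains no covariate for its prognostic value, and does not say whether the unadjusted or the final-model RR is the primary result.

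**The concern.** Change in estimate is meant to detect confounding. When infants are randomised individually, any baseline difference between arms is chance. The reasons to adjust are that a factor predicts the outcome or that randomisation was stratified by it. The 5% rule tests neither. A strong predictor that happens to be balanced is dropped, and centre, which the separate lists keep balanced, could hardly ever qualify.

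Three things are at stake:

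- **Precision.** Power for severe illness has little slack.
- **Pre-specification.** The covariate set is settled only after seeing how each candidate moves the treatment effect, and the two primary outcomes could end up with different sets.
- **Candidate variables.** Nothing in the rule restricts candidates to variables fixed before allocation. The list includes prelacteal feeds, time of breastfeeding initiation, receipt of colostrum and BCG vaccination, all of which can arise after allocation.

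**Working it through.** **Inputs from the protocol article (Sample size).** Total 4,760 with 5% attrition, so 4,760 × 0.95 = 4,522 evaluable, or 2,261 per arm. Control risk is 6% for severe illness and 11.5% for omphalitis, with a 30% relative reduction (RR 0.7). Two-sided 5% is assumed because sidedness is not stated.

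**The plan's own power figures.** At 2,261 per arm, 6% against 4.2% gives 78.6% power (stated 80%), and 11.5% against 8.05% gives 97.4% (stated 96%). Both are close, and this point disputes neither.

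**Assumptions.** The article gives no covariate effects, so those below are assumed and shown as a range. The estimate in the rule is read as the treatment RR. Candidates are screened one at a time against the unadjusted model, because no screening order is stated.

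**How often could chance imbalance trigger the rule?**

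*Standardised covariate.* The SD of the between-arm difference is 2/√4,522 = 0.0297. The shift in log RR is about β × difference, and the threshold is ln 1.05 = 0.0488.

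- RR 1.5 per SD: SD of shift 0.405 × 0.0297 = 0.0121; probability about 0.005%
- RR 2 per SD: 0.693 × 0.0297 = 0.0206; about 1.8%
- RR 2.5 per SD: 0.916 × 0.0297 = 0.0272; about 7.3%

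*Binary covariate, prevalence q, risk ratio R.* The shift is about d(R − 1)/(1 + q(R − 1)), where d is the difference in prevalence. With q = 0.10 the SD of d is √(2 × 0.1 × 0.9/2,261) = 0.0089.

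- R = 2: needs d = 0.05 × 1.1/1 = 5.5 points; probability about 7 × 10⁻¹⁰
- R = 3: needs 0.05 × 1.2/2 = 3.0 points; about 0.08%
- R = 4: needs 0.05 × 1.3/3 = 2.2 points; about 1.5%

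**What does the rule give up?** Trials of 4,522 infants with 20 candidate covariates were simulated at RR 0.7. Log-link Poisson with robust standard errors stood in for log-binomial in the three binary-covariate rows.

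| Assumed covariates | Outcome | SE of log RR, unadjusted | SE, fixed adjustment | Fall |
|---|---|---|---|---|
| Moderate, binary (RR 1.2–2) | Severe illness | 0.1311 | 0.1301 | 0.8% |
| Five with RR 1.5 per SD | Severe illness | 0.1316 | 0.1275 | 3.1% |
| Strong, binary (several RR 3–4) | Severe illness | 0.1315 | 0.1262 | 4.0% |
| Strong, binary | Omphalitis | 0.0935 | 0.0877 | 6.2% |

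The rule retained no covariate in any trial in the first two rows. With strong covariates it retained something in about 1–5% of trials across the null and RR 0.7 runs. Its SE for severe illness was then 0.1314, almost the unadjusted value.

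**In power terms, severe illness.** Power is about Φ(|ln 0.7|/SE − 1.96), with |ln 0.7| = 0.3567.

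- Moderate: 0.3567/0.1311 = 2.721 gives 77.7%; 0.3567/0.1301 = 2.742 gives 78.3%
- Strong: 0.3567/0.1315 = 2.712 gives 77.4%; 0.3567/0.1262 = 2.826 gives 80.7%

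Simulated rejection with strong covariates (450 trials) was 77.1% unadjusted, 77.3% under the rule and 80.9% with fixed adjustment.

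**Type I error.** Over 450 null trials with strong covariates, rejection was 5.8% unadjusted, 5.6% under the rule and 6.4% with fixed adjustment. The Monte Carlo SE is √(0.05 × 0.95/450) = 1.0 point, so all three are compatible with 5%.

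**Not quantified.** The article gives no centre-specific risks, so the gain from adjusting for centre cannot be sized. No shift from a post-allocation variable was computed.

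**The case against.** The strongest reply is that the rule almost never acts. If it retains nothing, the final model is simply the unadjusted RR, which is valid under randomisation and a legitimate primary analysis. Leaving precision unused is not an error, and the size of the gain depends on invented covariate effects. The threshold is numerical and the collected variables are listed, so discretion is narrower than it looks. The article does not call the final model primary, and a condensed article may leave that to the analysis plan.

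Most of this stands, and it limits the point. A reader might infer that the reported RR will be materially data-selected or biased, or that its significance test is inflated; the calculations show neither. Nor do the documents show that the rule would in practice retain a post-allocation variable. The section speaks of baseline characteristics, and the fault is only that the wording does not exclude such variables. The statement under Measurements that the study is unblinded is explained by the comparison arm's cord-care advice; it does not establish that the analysts see allocation.

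Two things survive. The article does not merely omit detail: it states a retention rule of the wrong kind, and an analysis plan that followed it would inherit the fault. And when the rule does act, outcome data decide the model. Making the unadjusted RR primary would cure that second fault, but would still leave out centre and the prognostic factors.

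**Conclusion.** The point holds as a should-fix. The 5% rule is the wrong criterion for choosing covariates here, and nothing else in the article offsets it. Its usual result is a valid unadjusted RR that is somewhat less precise than it could be. At the planned effect, fixed adjustment lowers the SE by about 1% with moderate covariates and about 3–6% with strong ones. For severe illness that is under one power point to about three. These figures rest on assumed, independent covariates and one-at-a-time screening. The secondary faults, a covariate set that depends on outcome data and no bar on post-allocation variables, are faults of specification with no demonstrated effect on the result. Confidence is high that the rule is unsuited to the design, and lower on the size of the loss.

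**What to change.** Delete the 5% rule, and do not choose covariates from the baseline comparison. Before outcome data are seen:

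- Name the primary model for both outcomes: log-link regression on arm, centre and a short fixed list of pre-randomisation prognostic factors, kept whatever they do to the estimate. Birth weight, gestational age and singleton or multiple birth are examples; the investigators should choose on prior knowledge of prognosis.
- State that variables that can arise after allocation are not eligible.
- Report the unadjusted RR alongside.
- Name modified Poisson regression with robust standard errors as the fallback if the log-binomial model does not converge.

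The cost is one paragraph of analysis text and a stated way of handling a few missing covariate values. Centre is known from randomisation and the example factors are already being collected, so no extra infants, visits or data are needed.

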**Fig. 2 Fig2:**
[figure not shown]
Flow chart of study participants

Subgroup analysis: subgroup analyses will be conducted. Associations between a single cord cleansing with 4% CHX and omphalitis will be stratified on relevant variables such as gestational age (±37 weeks (completed) of gestation) and birth weight (±2.5 kg). If substantial stratum-specific differences in effects are observed, we will proceed with analyses to identify effect measure modification. This may provide insight into possible interaction between the intervention and individual level as well as group- level contextual variables. Such effect measure modification analysis may provide potential causal explanations for our findings.

Equity impact analysis: further secondary analysis will compare the effectiveness of the intervention across strata of education levels, wealth quintiles and residence in order to assess the impact of the intervention on health and economic equity. All the data required for this analysis will be collected prospectively and, if the sample size allows, we shall estimate the effects of focusing this intervention on the most vulnerable groups. The Concentration Index, a bivariate measure of the distribution of important outcomes, will be used to measure any improved equity in outcomes.

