**Methods:**

The CHX study is a facility-based, individually randomized controlled trial that will be conducted among 4760 newborns in Uganda. The primary outcomes are severe illness and omphalitis during the neonatal period. Analysis will be by intention-to-treat.

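### Effect-modification analysis for omphalitis is run only after stratum differences look substantial, so any interaction result it yields is selected and cannot be read at its nominal level

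*Protocol article*

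**What the plan says.** The rule is in the subgroup paragraph of the Data analyses section of the protocol article.

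- **Outcome.** "Associations between a single cord cleansing with 4% CHX and omphalitis will be stratified". Severe illness, the other primary outcome, is not mentioned in this paragraph.
- **Factors.** The associations "will be stratified on relevant variables such as gestational age", cut at 37 completed weeks, and birth weight, cut at 2.5 kg. These are the only two factors named with cut-points.
- **Trigger.** "If substantial stratum-specific differences in effects are observed, we will proceed with analyses to identify effect measure modification". The paragraph does not say how large a difference counts, or whether the follow-on analysis is a formal test. The same section does put a figure on a substantial change when it selects confounders (more than 5%), but not here.
- **Use.** "This may provide insight into possible interaction between the intervention and individual level as well as group- level contextual variables". And: "Such effect measure modification analysis may provide potential causal explanations for our findings".

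A separate equity paragraph says that "further secondary analysis will compare the effectiveness of the intervention across strata of education levels, wealth quintiles and residence". That comparison has no trigger, and it names neither an outcome nor an interaction test, so it does not change the subgroup rule.

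**The concern.** Whether an interaction is examined at all depends on the data that the interaction test would use. A factor whose strata look alike yields no interaction result; a factor whose strata look different yields one. The interaction estimates and p-values that reach the report have therefore already been filtered for size, and a reader who takes p<0.05 at face value will be misled about how surprising it is.

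The two named factors are likely to have one small stratum each (preterm, low birth weight), and small strata give noisy RRs, so the filter will often be passed by chance. The paragraph also hopes for causal explanations from this analysis. At stake is how subgroup results for omphalitis are read, not the main treatment comparison.

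**Working it through.** **Inputs from the protocol article (Sample size, Randomization, Data analyses).** Total N 4760, 5% attrition, 1:1 allocation, control risk of omphalitis 11.5%, 30% relative reduction (RR 0.70, so 8.05% with chlorhexidine), type 1 error 5% (taken as two-sided), RRs from log-binomial regression. Evaluable per arm: 4760 × 0.95 / 2 = 2261.

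**The plan's own figure.** Power for omphalitis is stated as 96%. With the pooled-variance formula for two proportions:
- mean risk = (0.115 + 0.0805)/2 = 0.09775; null SE = √(2 × 0.09775 × 0.90225 / 2261) = 0.00883
- alternative SE = √((0.115 × 0.885 + 0.0805 × 0.9195)/2261) = 0.00882
- power = Φ((0.0345 − 1.96 × 0.00883)/0.00882) = 97.4%

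This is within 2 points of the stated value, so the inputs are understood as intended.

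**Assumptions.** The article gives neither the stratum shares nor the size of a substantial difference. I take a smaller stratum of 10% (226 and 2,035 per arm) and a 1.5-fold trigger, and show ranges for both.

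**Precision of the comparison between strata.** The variance of the difference in log RR is the sum of (1 − p)/(np) over the four arm-by-stratum cells:
- 0.9195/(226 × 0.0805) = 0.0505
- 0.885/(226 × 0.115) = 0.0341
- 0.9195/(2035 × 0.0805) = 0.0056
- 0.885/(2035 × 0.115) = 0.0038

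The sum is 0.0940, so SE = 0.307.

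**How often the strata look different by chance.** With a true RR of 0.70 in both strata, the two observed RRs differ by a factor of at least 1.25 in 47% of trials (ln 1.25 / 0.307 = 0.73) and by at least 1.43 in 25% (ln(1/0.7) / 0.307 = 1.16).

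**What a formal test needs.** p<0.05 requires the RRs to differ by a factor of about exp(1.96 × 0.307) = 1.82. Any such difference already exceeds a trigger of 1.25, 1.43 or 1.5.

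**Simulation** (400,000 trials per setting, same true RR of 0.70 in both strata, 1.5-fold trigger, Wald test on log RR):

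| Smaller stratum | Trigger met | p<0.05, all trials | p<0.05, given trigger |
|---|---|---|---|
| 5% | 35% | 4.1% | 12% |
| 10% | 20% | 4.7% | 24% |
| 15% | 12% | 4.9% | 40% |
| 50% | 3% | 5.0% | 100% |

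At a 10% share the two readings are linked by 0.196 × 0.238 = 0.047. The conditional figure depends heavily on the undefined threshold: at that share it is 8% for a 1.2-fold trigger and 92% for a 2-fold trigger.

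**Power.** For a true 0.70 ratio of RRs at a 10% share, power is Φ(1.16 − 1.96) = 21%. The ratio detectable with 80% power is about 2.4 at a 10% share and 1.7 at 50%.

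**The case against.** The strongest reply is that the trigger does no harm to the error rate. At a 10% share, every result that would reach p<0.05 exceeds a 1.5-fold trigger anyway, so the false-positive interactions are the same ones that would arise if every term were fitted. That is correct. A reader might infer from the conditional wording that the rule inflates the false-positive rate of a formal interaction test, but the third column of the table shows that it does not. Nor do the 47% and 25% measure false claims of effect modification. They say how often strata look different by chance, and fitting every term leaves them, and the 21% power, unchanged.

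A reader might also infer that the plan treats chance differences as causal. The text does not support that: it requires a second analytic step and says only that this may provide potential explanations. It also ties no decision on use of chlorhexidine to birth weight or gestational age.

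The open list of factors is weak ground too, because closing such a list is usual analysis-plan content and this is a condensed article. Leaving severe illness out is defensible. At its assumed 6% control risk and a 10% share, the SE of the difference in log RR is 0.435, and power for a 0.70 ratio falls to 13%.

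What survives is the rule the article does fix: interaction results are produced, and so reported, only after a favourable look at the strata, with no stated threshold and no stated test.

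**Conclusion.** The point holds as one about selective production and reporting of interaction results for omphalitis. With an assumed 10% smaller stratum and an assumed 1.5-fold trigger, about 24% of triggered tests would show p<0.05 with no true difference between strata, although the rate over all trials stays at about 5% per variable. The 24% moves widely with the assumed share and threshold, and the article fixes neither. If the follow-on analysis is descriptive rather than a formal test, chance differences that meet the trigger (20% of trials under the same assumptions, 3% to 35% across the shares examined) could be presented as effect modification. Both primary comparisons are untouched and the interpretive wording is cautious, so this is a minor improvement to a secondary analysis.

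**What to change.** Remove the condition. For the two named factors, gestational age at 37 weeks and birth weight at 2.5 kg, fit the arm-by-factor term in the log-binomial model for omphalitis whatever the stratum results. Report every stratum RR with its confidence interval, together with the interaction estimate (the ratio of RRs), its interval and its p-value. Label any further factor in this paragraph, and any causal reading of a difference, as exploratory. Extending the same analysis to severe illness is optional; if it is done, its low power should be stated.

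The cost is a change of wording and a few extra model fits, with no effect on conduct or sample size. The price in interpretation is that the interaction results will often be inconclusive, and the report should say so rather than take a non-significant term as evidence of a uniform effect.
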